## Results

Recruitment for the trial started in March 2013 and is expected to continue until April 2015. No major changes have been made to the protocol. However, due to an error in the randomization algorithm between January 14, 2014, and July 15, 2014, allocation was dependent on the number of participants who were allocated at once. This in turn was completely random. Consequently, 10 participants were allocated directly to the AAF group; 4 other participants were divided equally between the 2 experimental interventions; and 15 accounts (of which, 1 was a dummy account) were equally divided between the 3 groups. None of the researchers were aware of this error, as this allocation could very well have simply been the result of the “roll the dice” scenario that should have been applied. How many participants were allocated at once was not the subject of the researchers’ decision-making. Therefore, we argue that allocation has still been random and, accordingly, data for all considered participants will be processed as originally planned.

At the time of this writing in January 2015, 269 patients have registered at the project website. Of these, 111 have been officially included in the study, 50 were excluded from participation, and 35 withdrew before their eligibility was checked. The remaining patients are still in the enrollment phase. The main reason for exclusion so far has been a score lower than 35 on the CIS fatigue severity subscale (60%). Furthermore 11% did not meet the psychiatric stability requirement, 8% were younger than 18 at the time of cancer diagnosis, and 8% were still receiving cancer treatment.

Current group sizes as of January 2015 for participants in the first semester are 36 (AAF), 24 (eMBCT), and 32 (control). However, 19 participants have not yet been randomized. Initial responses to the primary research question are expected to be available by the end of 2015.

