#### Randomization

If the eligibility-criteria are met, the researcher confirms the participant’s enrollment. Subsequently, the activity sensor is given to the participant and its setup is explained in a face-to-face meeting in the participant’s home or another mutually convenient location. The second baseline assessment starts (T0b), followed by randomization of the participant to 1 of the 3 conditions by a script embedded in the researchers’ Web portal and uses the random function of php (rand(1,3)) [50]. The researchers can neither influence nor predict the outcome of the randomization process. Subsequently, the researcher emails the participant about the outcome of randomization, requests the participant to complete the third baseline assessment (T0c), and assigns the participant to a therapist in case the participant has been randomized to an experimental condition. Participants who do not fill out T0c are considered as not being included. The allocation of a therapist is based on current availability of the therapists who are involved in the trial.

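### For six months in 2014 the arm depended on batch size, not on the planned one-in-three draw, yet the article calls this allocation random and commits to unchanged analysis

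*Protocol article*

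**What the plan says.** The Randomization section describes a script in the researchers' portal that draws an integer from 1 to 3 for each participant, which gives one chance in three per arm. It adds: "The researchers can neither influence nor predict the outcome of the randomization process".

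The Results section reports an algorithm error between 14 January and 15 July 2014, during which "allocation was dependent on the number of participants who were allocated at once". For the batches that sent nobody to control, it says "10 participants were allocated directly to the AAF group; 4 other participants were divided equally between the 2 experimental interventions". The remaining batches are covered separately, where the article reports that "15 accounts (of which, 1 was a dummy account) were equally divided between the 3 groups". The arm of the dummy account is not stated.

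Two sentences defend the allocation. Of the number allocated at once, the article says "This in turn was completely random", and later "How many participants were allocated at once was not the subject of the researchers’ decision-making". It concludes: "Therefore, we argue that allocation has still been random and, accordingly, data for all considered participants will be processed as originally planned". It also says that the researchers were unaware of the error at the time.

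The general safeguards are elsewhere. Descriptives plans baseline comparisons with covariate adjustment and a CONSORT flow diagram. Step 1 of the effectiveness analysis constrains the intercept and the pre-intervention slope to be equal across arms and checks that assumption. A statistician blind to allocation tests the primary hypothesis. None of these is specific to the error window.

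**The concern.** Both primary contrasts (AAF and eMBCT against control) rest on randomized comparability. For half of the window's participants, the batch they fell into sent nobody to control. How many people are processed together is an operational count. It may be unpredictable, but the article does not describe how batches formed, and its statement that batch size was random stands alone.

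At stake is whether the AAF contrast, and to a smaller extent the eMBCT contrast, partly reflects who enrolled in early 2014 and not the intervention. The equality constraints in the growth model rely on randomization, and the checks on them can detect only measured pre-treatment differences. This is not a detail left to a fuller document: the article states the decision to analyse these participants without any change.

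**Working it through.** **Inputs**, all from Results unless noted: 10 participants to AAF only; 4 split equally between AAF and eMBCT; 15 accounts split equally over three arms, one a dummy; January 2015 group sizes 36 AAF, 24 eMBCT, 32 control; 111 included, 19 not yet randomized. Planned probability 1/3 per arm (Randomization). Planned total 330 (Power Analyses).

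**Reproducing the article's count.** 36 + 24 + 32 = 92, and 111 − 19 = 92. The figures agree.

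**Window by arm.**
- AAF: 10 + 2 + 5 = 17 accounts. eMBCT: 2 + 5 = 7. Control: 5. Total 29.
- Without the dummy there are 28 participants, split 16/7/5, 17/6/5 or 17/7/4 according to the dummy's arm.
- Batches that sent nobody to control: 10 + 4 = 14 participants, of whom 10 + 2 = 12 AAF, 2 eMBCT, 0 control.

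**Shares**, assuming all window participants are among the 92:
- 14/28 = 50% of window participants
- 14/92 = 15% of those randomized
- 12/36 = 33% of AAF
- 2/24 = 8% of eMBCT

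**Association of arm with period** (ranges reflect the dummy's unknown arm):

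| | AAF | eMBCT | Control | Total |
|---|---|---|---|---|
| In window | 16–17 (57–61%) | 6–7 (21–25%) | 4–5 (14–18%) | 28 |
| Outside window | 19–20 (30–31%) | 17–18 (27–28%) | 27–28 (42–44%) | 64 |
| Window share of arm | 44–47% | 25–29% | 12.5–16% | |

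**Departure from one third per arm.** For the 29 accounts, with 29/3 = 9.67 expected per arm, chi-square = (17² + 7² + 5²)/9.67 − 29 = 37.55 − 29 = 8.55 on 2 df, p = 0.014. For the 28 participants the exact multinomial p is 0.010 to 0.034. These values confirm a departure that the article already admits. They say nothing about bias.

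**Bias.** If the 12 AAF participants differed from the rest of the arm by d points in expected change on CIS fatigue severity, the AAF mean would shift by (12/n) × d. The document gives no value for d. Taking 2 to 5 points purely as an assumption, the shift is 0.7 to 1.7 points at n = 36 and 0.2 to 0.5 points at n = 330/3 = 110. The sign is unknown.

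**Sets for sensitivity analysis at January 2015 counts.**
- Without the 14: 36 − 12 = 24, 24 − 2 = 22, and 32, total 78.
- Without all 28: 92 − 28 = 64, split 19–20 / 17–18 / 27–28.

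**The case against.** The error is openly disclosed with dates and counts. The researchers did not know of it, which makes deliberate selection unlikely. If batch size was unrelated to the participant, each person had, before the batch formed, some chance of a batch that included control. The analysis plan also has baseline comparisons, a check of the equality constraints and a blinded statistician.

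Much of this stands, and it rules out several stronger readings.
- A reader might infer that the 14 had no chance of control at all. That is so only conditional on batch size.
- A reader might infer that the article defends the allocation as compatible with the intended dice-roll process. That remark explains only why nobody noticed. The defence is the pair of sentences on batch size, so small p-values against one third per arm do not answer it.
- A reader might conclude that the claim of randomness is shown to be false. The document shows only that it is unsupported.
- A reader might want the 14 removed from the primary set. That departs from the stated intention-to-treat basis, removes 12 AAF and 2 eMBCT but no control participants, and cuts AAF by a third at January 2015 counts. It also trusts the 14 participants in the three-arm batches, although the article does not say that order within those batches was random.

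The objection does not rescue the plan to process everything unchanged. Even on the authors' own account, allocation probabilities inside the window differed from those outside it. The general checks do not isolate these participants.

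**Conclusion.** The concern holds in a limited form. Allocation in the window did not follow the planned one-in-three randomization, the claim that batch size was random has no stated support, and arm is associated with calendar period: window participants are 44–47% of AAF but 12.5–16% of control.

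The shares of 15% (all randomized) and 33% (AAF) assume that everyone allocated in the window is among the 92. The article does not say so, and the Randomization section treats people who skip the T0c assessment as not included. The shares would fall as recruitment continues: at the planned 330, the 14 would be 14/330 = 4% of the total and the 12 would be 12/110 = 11% of an equal AAF arm. The final size is not known from the document.

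A reader might infer that the primary estimate is biased by a stated number of points. The document does not support that: any such figure rests on an assumed difference, and neither the size nor the direction of bias can be calculated.

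**What to change.** 1. Keep the intention-to-treat analysis of all participants as primary.
2. Before any data are analysed, pre-specify two sensitivity analyses of the primary contrasts: one without the 14 participants whose batches sent nobody to control (24/22/32 at January 2015 counts), and one without all 28 window participants (64 remain).
3. In Results, replace the conclusion that allocation was still random with a statement that allocation in the window did not follow the planned one-in-three randomization. If there is evidence that batch size was unrelated to the participants, describe how batches formed.
4. In the Randomization section, qualify the statement on influence and prediction so that it describes the intended procedure and points to the window.
5. Show window participants by arm in the flow diagram, and state the dummy account's arm.

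The cost is two extra model runs and a less favourable description of the allocation. The primary set loses nobody. The Discussion says that the article was submitted before any data were analysed, so at that point these analyses could still be fixed without knowledge of the results.

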## Discussion

### Principal Findings

This paper has described the design, hypotheses and analysis plan of a randomized controlled trial in order to study the effectiveness, mediation, and effect predictors of 2 Internet-based interventions for CCRF. Although recruitment and inclusion have already started, publishing the analysis plan is of great value because it will help to prevent outcome reporting bias [110] and adds validity information to the final studies [111].

By using multiple assessments during the intervention, the proposed trial design is suitable for studying the chronological development of both potential mediators and fatigue. That has 2 main advantages. Firstly, the data will be suitable for analyses that allow for variation in the individual fatigue trajectories. We do not expect that either of the interventions that have been included in the trial will be beneficial for all participants: our study sample will be highly heterogeneous considering for example tumor and treatment types. Therefore, the analyses on individual growth trajectories can acknowledge that expectation and test that hypothesis. This will substantiate the interpretation of the results on effectiveness and will be an important first step in identifying what works for whom. Secondly, this study design enables us to use a fully longitudinal mediation analysis, at least for the most important factors, rather than using indirect effects analysis in cross-sectional mediation analysis.

Another important feature of the proposed design is that by comparing 2 different interventions with an active control group, therapy-specific elements of the interventions can be distillated from the data acquired during this trial. This advantage counts for both the effect predictors and the mediators. Knowledge about such differentiating factors can and should be used to better inform patients with CCRF and to improve allocation of patients with CCRF to suitable interventions. As a result, an increase in the overall effectiveness of relevant interventions can be established.

In this paper, we have presented the trial design, our hypotheses, and a detailed analysis plan. In accordance with good clinical practice, and to avoid outcome reporting bias, this paper was submitted before any of the data was analyzed. All methods are now openly predetermined, therefore any future publication describing this trial can be valued reliably on its quality.

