### Effectiveness

#### Overview

Our primary question is whether both interventions are effective in reducing fatigue. Therefore, the interventions will be compared to an active control group in a randomized controlled trial. The advantage of this design, as compared to a waiting-list control group, is that we can control for nonspecific influences of the trial, such as receiving attention. Also, we expect that in an active control group, fewer participants will drop out than in a waiting-list control group.

Usually, results of interventions are presented in terms of an average improvement of the relevant outcome measure. However, practice shows that individuals benefit differently from interventions [41]. Therefore, the proposed trial will aim to identify individual fatigue trajectories, since that seems to be more informative and helpful in improving health care provisions for CCRF-patients than just presenting averages.

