#### Core Analysis

##### Effectiveness

###### Overview

Five steps will be taken to evaluate the effectiveness of both interventions, which are explained here in a generic way. The specific hypotheses on the effectiveness of the interventions in our study are shown in Textbox 1.

Hypotheses on effectiveness.
*Primary outcome*
In both experimental conditions:Fatigue severitydecreases during the intervention, andremains decreased after 6 months.After 6 months, fatigue severity has decreased significantly more compared to the control condition.After 6 months, more participants show a clinically relevant reduction of fatigue severity compared to the control condition. A patient is considered clinically improved if he or she has a reliable change index of more than 1.96, according to the reliable change index, and the end score has to be within the normal range, that is a score < 1 standard deviation above the mean of a normative group [94] (ie, a score < 30.4 on the CIS fatigue severity subscale [51]).
*Secondary outcomes*
For both interventions we expect that:After 6 months, mental health and work ability have improved more than in the control condition.After 12 months, fatigue severity, work ability, and mental health remain improved in both intervention groups.Improvements in mental health and work ability after 6 and 12 months are related to reductions in fatigue severity.Return to work and reduced absenteeism will be studied as explorative outcomes.

###### Step 1

Overall effectiveness will be tested in an intention-to-treat analysis by a multiple group latent growth model [79] using data from the first semester. This technique allows individuals to have an individual growth trajectory over time and compensates for missing data in an elegant way.

Since different growth patterns are expected for the pre-intervention period, the intervention period, and the post-intervention period, we will apply piecewise growth modeling so that a slope factor will be estimated for each of the 3 periods (Figure 4). Initial intercepts will be configured to represent the T0b score. This intercept and the pre-intervention slope factor will be constrained to be equal between all 3 conditions (and this assumption will be checked), whereas the subsequent slope factors will be estimated separately for the 3 conditions.

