The fit of the piecewise model will be compared with a quadratic model. In the quadratic model, the entire first semester is modeled with 1 slope factor and 1 quadratic factor for each of the 3 conditions and an intercept that represents T0b and is constrained similarly to the piecewise model.

Both models will be run both with and without using time-varying loadings in order to check whether corrections should be made for differences in timings between the questionnaires. Growth factor estimates and model fits for all 4 models will be reported (Table 5).

Neither the participants nor the researchers ([name] and MW) are blinded to allocation. Therefore, an independent statistician ([name]) who is blind to the allocation will test the primary hypothesis.

The same procedure will be followed for the secondary outcomes, except that the initial intercept of mental health will represent T0a, rather than T0b, because T0b does not include an assessment of mental health.

Results of frequentist analyses will be reported by *P*-values (significant in case <.05) and with 95% confidence intervals. Parameter estimates of models by means of Bayesian estimators will be reported with 95% central credibility intervals.

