**Figure 4 figure4:**
[figure not shown]
Simplified representation of a piecewise linear latent growth model, with latent intercept factor (I), latent slope factors preintervention (S(pre)), during the intervention (S(int)), and postintervention (S(post)), and 7 indicators Y. Error terms, correlation coefficients, and covariances are left out.

**Table 5 table5:** Growth factor estimates of 4 different latent growth models.

	Fixed loadings	Time-varying loadings
Piecewise, linear	Mean: I, S(pre), S(int), S(post) Variance: I, S(pre), S(int), S(post)	Mean: I, S(pre), S(int), S(post) Variance: I, S(pre), S(int), S(post)
Quadratic	Mean: I, S, Q Variance: I, S, Q	Mean: I, S, Q Variance: I, S, Q

###### Step 2

The effect size of both experimental interventions will be calculated according to recommendations in Feingold (2009) [95] for both primary and secondary outcomes.

###### Step 3

The proportion of participants who make clinically relevant progress on the primary outcome will be calculated for all 3 conditions; again, in an intention-to-treat analysis. Percentages and standard deviations of the reliable change index will be presented.

###### Step 4

A latent growth model will be built of the primary outcome, in which the outcome measures that have been measured at T3 will also be included, as distal outcomes of changes in the primary outcome during the first semester.

###### Step 5

A growth mixture model (GMM) will be used to further explore differences between individuals, and more specifically to identify subpopulations (latent classes) with homogeneous growth trajectories of the primary outcome within the experimental groups. The Bayesian information criterion will be used for model selection [96].

If convergence considerations allow, this model will be adjusted to allow covariance of the growth factors in order to acknowledge individual variation around the estimated growth trajectories. The trace plots will be inspected to check whether the models have converged to global solutions and a set of diverse starting values will be used. For more information on these analyses, we refer to an introduction to GMM and latent class growth analysis by Jung and Wickrama [97] and examples of similar analyses in the field of Internet interventions [98] and cancer patients [41].

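### The plan says individual-trajectory analyses can test whether everyone benefits, but no step compares the spread of trajectories with control

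*Protocol article*

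**What the plan says.** The Introduction (Effectiveness, Overview) justifies looking at individual trajectories on the ground that "practice shows that individuals benefit differently from interventions". The Discussion (Principal Findings) states the expectation outright: "We do not expect that either of the interventions that have been included in the trial will be beneficial for all participants". It then says that "the analyses on individual growth trajectories can acknowledge that expectation and test that hypothesis", and presents this as a first step towards knowing what works for whom.

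The steps that bear on this are:

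- **Step 1.** "Overall effectiveness will be tested in an intention-to-treat analysis by a multiple group latent growth model". After the pre-intervention period, "the subsequent slope factors will be estimated separately for the 3 conditions". On reporting: "Growth factor estimates and model fits for all 4 models will be reported (Table 5"). For the piecewise model that table lists "Mean: I, S(pre), S(int), S(post) Variance: I, S(pre), S(int), S(post").
- **Step 3.** The proportion with clinically relevant progress is calculated in all three arms.
- **Step 5.** A growth mixture model looks for latent classes of fatigue trajectory in the experimental groups. The Bayesian information criterion (BIC) selects the model.
- **Step 8.** Named predictors act on the slope, with coefficients free in all three groups. Those with the highest loadings are compared between conditions.
- **Step 9.** Predictors are regressed on the Step 5 classes, separately for each experimental condition.

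Textbox 1 contains no hypothesis about the variance of slopes.

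**The concern.** Benefit is the difference between a patient's course on treatment and the course that patient would have had without it. One treated trajectory does not show that difference. If natural courses vary, treated trajectories will vary too, even when the treatment shifts every patient by the same amount. The concurrent control arm shows how much spread to expect without the experimental treatment, so it is the natural reference for the expectation in the Discussion.

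The plan does not set that comparison up. Steps 5 and 9, which describe individual differences most directly, leave the control arm out. Step 1 estimates the variances that are needed but specifies no contrast between arms. The Discussion's claim of a test therefore has no step behind it, except for predictors that happen to be measured.

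The Discussion says that knowledge of differentiating factors should inform patients and improve their allocation to interventions. Classes that mirror natural course could be carried into that use as if they were evidence of who benefits.

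**Working it through.** **1. Which steps use control, and for what**

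| Step | Control included? | Compares spread of trajectories between arms? |
|---|---|---|
| 1, growth model | Yes, own slopes | No; variances are listed for reporting only |
| 3, responder proportions | Yes | No; proportions shift even if the effect is identical for all |
| 5, mixture model | No | No |
| 8, predictors of slope | Yes | No; predictor-by-arm effects for measured factors |
| 9, predictors of class | No | No |

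**2. Inputs for the illustration**

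From the Power Analyses section: 77 per experimental arm and 94 in control at T2. From the Results: 36 (AAF) and 32 (control) in January 2015. From Step 1: significance at .05, taken as two-sided for the arm comparison. The article gives no slope or residual SD. Assumed: residual SD 4 CIS points; natural 9-week change SD 3, 5 or 7; a mean effect of -4; assessments at weeks 0, 3, 6, 9 and 11, with the slope ending at week 9.

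Error variance of a patient's estimated 9-week change: the times count as 0, 3, 6, 9, 9, with mean 5.4 and sum of squares about the mean 61.2. So 81 × 16 / 61.2 = 21.2.

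**3. Same effect for every patient**

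Within the treated arm, the ratio of estimated-slope variance to error is (natural variance + 21.2) / 21.2. A one-sided F test on 76 and 231 degrees of freedom then rejects zero slope variance as follows:

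| Natural SD | Ratio | Within-arm rejection | Rejection versus control | True course rising, Φ(-4/SD) |
|---|---|---|---|---|
| 3 | 30.2/21.2 = 1.42 | 61% | 5% | 9% |
| 5 | 46.2/21.2 = 2.18 | 99% | 5% | 21% |
| 7 | 70.2/21.2 = 3.31 | over 99.9% | 5% | 28% |

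The last column takes mean natural change as zero. A simulation with other assumptions (change scores, slope SD 3, 6 and 9, constant effect of 5 points) agrees: 47%, 99.6% and 100% within arm, against 4.7%, 4.8% and 3.7% between arms by Levene's test.

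**4. Latent classes**

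The same constant effect was simulated over six occasions, and one class was compared with two by BIC, with no variance allowed within classes. When patients differed in intercept or slope, two classes won in 100 of 100 runs in the experimental arm and in 100 of 100 in control. When they did not differ, two classes won in 1 of 100 in each arm. Step 5 would allow growth-factor covariance if convergence permits, which would reduce this over-extraction. It would not supply a control reference.

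**5. What a between-arm contrast could detect**

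The expected ratio of estimated-slope variances is (natural variance + effect variance + 21.2) / (natural variance + 21.2), with effect and natural course taken as independent. At natural SD 5:

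- effect SD 3: (25 + 9 + 21.2) / 46.2 = 1.195; two-sided F-test power at 77 versus 94 is 13%.
- effect SD 6: (25 + 36 + 21.2) / 46.2 = 1.78; power is 75%, or 36% at 36 versus 32.

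For effect SD 6, power at 77 versus 94 is 95% at natural SD 3 and 47% at natural SD 7. An effect SD of 6 around a mean of -4 is extreme: Φ(-4/6) = 25% of patients would be made worse. In general, power at 77 versus 94 is 46% for a variance ratio of 1.5 and 89% for 2.0.

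**The case against.** The strongest reply is that the plan never commits the error. A reader might infer that natural variation will be reported as differential benefit, or that the hypothesis counts as confirmed whenever courses differ. The document does not support that. No passage makes a non-zero variance, a class solution or a rising trajectory the decision rule, and Step 5 is worded as exploration. What stands is a risk of misreading, created by a claimed test without a specified comparison.

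A reader might also infer that the control arm is not used for individual differences at all. That too goes too far. Step 1 models control slopes separately and lists growth-factor variances for reporting, so the comparison could be made from planned output. Step 8 compares predictor effects between conditions, which is a control-referenced look at what works for whom. Both points stand, and they narrow the concern. Step 8 nevertheless covers measured predictors only, and comparing the highest loadings is not a formal interaction test.

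Nor is it right that only spread beyond the control arm can support unequal benefit. A predictor-by-arm effect supports it without excess total variance. If effect and natural course are negatively correlated, spread can stay equal or shrink while benefit differs.

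Finally, the article says its plan is written in general terms, and a variance contrast is a detail that a fuller plan might hold. That would answer a complaint of omission. It does not answer a claim in the Discussion that the described analyses can test the hypothesis.

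**Conclusion.** The point holds in limited form. The Discussion says the individual-trajectory analyses can test that not everyone benefits, but Steps 5 and 9 have no control reference and no step compares the spread of trajectories between arms. Within-arm variation or classes can then be taken for unequal benefit when they may be natural course. Under the assumed SDs, with no differential benefit at all, a within-arm test of slope variance is positive in 61% to over 99.9% of trials, while a comparison with control stays near 5%.

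These figures are illustrations: the document gives no SDs, and it does not say that a within-arm test will be used in this way. The class result also depends on a model without within-class variance. The primary comparison of mean fatigue is not affected. The change is worth making because it is cheap and the claim concerns a stated aim, but it will not give a powerful test of unequal benefit.

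**What to change.** - **Step 1.** In the multiple-group model, prespecify for each intervention versus control the ratio of the between-patient SD of S(int), and of the T0b-to-T2 change, each with a 95% interval.
- **Steps 5 and 9.** Fit the Step 5 class model in the control arm as a reference before interpreting classes, or their predictors, as differential benefit.
- **Discussion, Principal Findings.** Say that variation or classes within a treated arm do not by themselves show unequal benefit; that evidence comes from control-referenced contrasts, either excess spread or the Step 8 predictor-by-arm effects; and that equal spread does not exclude unequal benefit.

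The cost is one contrast per intervention in a model already planned, one further class model, and a few sentences. The drawback is low precision (power of about 13% to 75% at 77 versus 94 for effect SD 3 to 6, with natural SD 5 and residual SD 4). The ratio should therefore be reported as an estimate with its interval, and a non-significant result should not be read as equal benefit.
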